**Sampling Plan**

Existing Data

*None*

Data collection procedures

*Population:* The participants will be healthcare workers (HCWs) employed at Sri Jagannath Heath Care and Research Centre, Dhanbad, Jharkhand, India. They are facing significant psychological stress during this COVID-19 pandemic, making them suitable candidates for the study aimed at assessing interventions for stress reduction.

*Recruitment:* Participants will be recruited by posting a call for participation on the internal email system and notice board of the hospital. This announcement will include all relevant information about the study, such as the nature of the interventions, expected commitment, and the informed consent form. No payments will be provided for participation.

*Inclusion and Exclusion Criteria:*

Inclusion Criteria: Participants will be aged 18 years or over and be currently employed HCWs at the hospital. They will also need to be available for the entire duration of the intervention (1 week) and follow-up (45 days post-intervention).

Exclusion Criteria: Participants with pre-existing diagnosed mental health conditions will be excluded to ensure that the study focuses on measuring the effect of the interventions on psychological distress caused by work-related stress during the pandemic, rather than on pre-existing disorders.

*Grouping:* After the eligible HCWs return the signed informed consent forms, they will be randomized into one of four groups (Control, Yoga, Gita, Yoga+Gita) using a chit-pull system, as previously described, in a 1:1:1:1 ratio.

*Study Timeline:* Recruitment will begin on October 25, 2021, and end on November 5, 2021. The baseline assessment (B-GAD7) will be administered on November 12, 2021. The interventions (Yoga, Gita, Yoga+Gita) will be conducted between November 13, 2021, and November 19, 2021. The immediate post-intervention GAD7 (IPI-GAD7) will be collected on November 20, 2021 (1 day post-intervention). The delayed post-intervention GAD7 (DPI-GAD7) will be administered on January 3, 2022 (45 days post-intervention).

*Intervention Details:* Participants in the intervention groups will attend daily 1-hour sessions for one week. The Yoga group will practice yoga for the entire hour. The Gita group will attend Bhagavad Gita lessons for one hour. The Yoga+Gita group will have 30 minutes of yoga followed by 30 minutes of Bhagavad Gita lessons. The Control group will not receive any intervention.

*Data Collection Process:* Psychological distress will be measured using the Generalized Anxiety Disorder-7 (GAD7) scale at three time points; Baseline (B-GAD7) - Administered before the interventions starts, Immediate Post-Intervention (IPI-GAD7) - Administered 1 day after the last intervention session, and Delayed Post-Intervention (DPI-GAD7) - Administered 45 days after the intervention. All data will be collected anonymously using only the participant identification numbers (PINs) to maintain confidentiality.

*Data Management:* The consent forms and a document linking participants’ names to their PINs will be securely stored and not accessible to the data analysis team or to the intervention coordination and data collection team. The data will include GAD7 scores and demographic information (age, gender, education level).

Sample size

*The sample size will be calculated to detect significant effects with 80% power to detect a minimum clinically important difference of 4 for the GAD7 with a standard deviation of 3.78 at the standard alpha error of 0.05. A dropout rate of 15% will be considered. PASS 2020, v20.0.6 will be used to calculate the sample size.*

Stopping rule

*None*

**Variables**

Manipulated variables

*None*

Measured variables

*The primary outcome variable is psychological distress, measured using the GAD7 scale at baseline, immediately post-intervention, and 45 days post-intervention. The main predictor variable is the intervention type (Control, Yoga, Gita, Yoga+Gita), and demographic covariates (age, gender, education) will also be collected. Continued practice is a follow-up variable to examine its impact on long-term outcomes.*

**Analysis Plan**

Statistical models

*Descriptive Statistics:* Before any inferential tests, we will compute descriptive statistics (mean ± standard deviation for continuous variables and frequencies/percentages for categorical variables) to describe the demographic characteristics (age, gender, education level) and baseline GAD7 scores for each group.

*Tests for Normality:* To determine the appropriate statistical tests, we will first assess the normality of the GAD7 scores using the Shapiro-Wilk test. If the data are normally distributed, we will proceed with parametric tests. If the data do not meet normality assumptions, we will use non-parametric alternatives.

*Primary Plan (Parametric Tests):*

Within-Group Comparisons: To examine changes in GAD7 scores over time (Baseline, Immediate Post-Intervention, and Delayed Post-Intervention) within each group, we will use repeated-measures ANOVA. If significant, we will conduct pairwise t-tests with Bonferroni correction to compare GAD7 scores between each pair of time points (e.g., Baseline vs. IPI-GAD7, Baseline vs. DPI-GAD7).

Across-Group Comparisons: To compare GAD7 scores between the four groups (Control, Yoga, Gita, Yoga+Gita) at each time point (Baseline, IPI-GAD7, DPI-GAD7), we will use one-way ANOVA. If significant differences are found, we will apply Tukey’s HSD for post-hoc pairwise comparisons between groups.

Subgroup Analysis (by Gender, Educational Attainment, and Continued Practice): For subgroup analyses, we will use two-way ANOVA to assess whether gender (male, female), education level (Bachelor’s vs. Master’s or higher), and continued practice (yes, no) influence GAD7 score changes over time or interact with the interventions.

Effect Size Calculations: Partial eta-squared (η²) will be calculated for repeated measures ANOVA and η² will be calculated for one-way ANOVA to estimate the effect sizes.

*Backup Plan (Non-Parametric Tests):*

Within-Group Comparisons: We will use the Friedman Test to compare GAD7 scores over time within each group (Baseline, IPI-GAD7, DPI-GAD7). If significant, we will perform pairwise comparisons using the Conover Test to identify specific differences between time points.

Across-Group Comparisons: To compare GAD7 scores across the four groups at each time point, we will use the Kruskal-Wallis Test. If significant, we will conduct the Dunn’s Test for pairwise group comparisons.

Subgroup Analysis (by Gender, Educational Attainment, and Continued Practice): For the gender, education, and continued practice subgroup analyses, we will use the Mann-Whitney U Test to compare GAD7 scores between subgroups at each time point.

Effect Size Calculations: We will compute the Kendall’s W for effect size in the Friedman test and η² for the Kruskal-Wallis test to estimate the effect sizes. Statistical Significance: For all tests, a two-tailed p-value < 0.05 will be considered statistically significant.

Transformations

*None*

Data exclusion

*Participants who miss any follow-up session (B-GAD7, IPI-GAD7, DPI-GAD7) will be excluded.*

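### A Shapiro-Wilk pretest on the GAD7 scores chooses between two analysis plans that are not equivalent, and near the scale's floor it can respond to the treatment effect

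*Protocol*

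**What the plan says.** Under Tests for Normality, the protocol's Analysis Plan begins with a pretest: "we will first assess the normality of the GAD7 scores using the Shapiro-Wilk test". Two branches follow: "If the data are normally distributed, we will proceed with parametric tests", and "If the data do not meet normality assumptions, we will use non-parametric alternatives". The Transformations entry is none, so there is no third route.

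- **Primary Plan.** Over time, "within each group, we will use repeated-measures ANOVA", followed by Bonferroni-corrected pairwise t-tests. Between groups, "at each time point (Baseline, IPI-GAD7, DPI-GAD7), we will use one-way ANOVA", with Tukey's HSD. For gender, education and continued practice, two-way ANOVA asks whether these factors "influence GAD7 score changes over time or interact with the interventions".
- **Backup Plan.** Friedman and Conover tests over time. Between groups, "To compare GAD7 scores across the four groups at each time point, we will use the Kruskal-Wallis Test", then Dunn's test. For the subgroups, "we will use the Mann-Whitney U Test to compare GAD7 scores between subgroups at each time point".

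The Sample size entry powers the trial at 80% for a 4-point GAD7 difference, with SD 3.78 and alpha 0.05. Study questions 7 and 8 ask whether gender and education moderate the effect of the interventions.

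**The concern.** A stated rule lets the trial's outcome data choose the trial's analysis. That raises three problems.

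1. **Quantity tested.** Repeated-measures ANOVA and paired t-tests rest on differences within a person. One-way ANOVA rests on errors within an arm. The text names the scores, not differences or residuals.
2. **Dependence on the effect.** GAD7 cannot go below zero. If an intervention pushes scores towards zero, the distribution skews and the pretest can fail because of the effect under study.
3. **Different questions.** The two plans do not estimate or test the same things, so the pretest result decides which study questions are answered.

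**Working it through.** **Inputs from the protocol.** Target difference 4, SD 3.78, power 80%, two-sided alpha 0.05, dropout 15%, four arms at 1:1:1:1 (Sampling Plan and Analysis Plan). The protocol prints no resulting sample size and no figure for the normality step, so there is no stated figure to reproduce.

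**Assumptions.** Whole scores from 0 to 21; normal scores rounded and clipped to that range; Shapiro-Wilk cut-off 0.05; baseline means of 8 to 14. The protocol gives none of these.

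**Size per arm.** The normal approximation is n = 2(1.960 + 0.842)² × 3.78² / 4² = 14.02, so 15. The exact t-test gives 16, which is used below. The standardised difference is 4/3.78 = 1.06 SD.

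**How often the pretest fails.** One post-intervention time point, arms pooled, 3,000 replicates:

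| Control mean | No effect | Three active arms lower by 4 |
|---|---|---|
| 8 | about 10% | 93% |
| 10 | about 9% | about 27% |
| 12 | about 8% | about 8% |
| 14 | about 17% | about 8% |

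If each arm is tested separately and any failure counts, the rate at mean 8 goes from about 21% to 62-64%. At mean 10 it hardly moves (22% to 25%).

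**What drives it.** With continuous, unbounded normal scores, pooled rejection is about 5% without an effect and 5-6% with one, at 15 to 25 per arm. A shift of 1.06 SD between arms therefore barely moves the test; the floor does. At mean 14 the ceiling works the other way.

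**Within-person comparisons.** Each person's own level cancels in a difference. Skewed person levels can make raw scores fail while the differences are normal. In an illustration with 16 people, skewed person effects and normal within-person errors, raw scores failed at one or both of two time points in 38% of samples. The differences failed in 5%, the nominal rate.

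**Would testing residuals cure it?** Not fully. On scores minus the arm mean, with 15 to 25 per arm, rejection at mean 8 still goes from 5-6% to 31-60%.

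**Cost to the overall group test.** Across 15 to 25 per arm and the means tried, choosing by pretest gives type I error of 4.0-6.2%. Always using ANOVA gives the same range in the same simulations. The largest power loss is about 4 points (83.4% to 79.1%, at 15 per arm and 8 versus 4).

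**The branches side by side.** The Primary Plan's two-way ANOVA includes the interaction of gender or education with intervention, which is what questions 7 and 8 ask. The Backup Plan's Mann-Whitney tests compare, for example, men with women at each time point. They contain no intervention term and cannot show moderation. The 4-point sample-size target is a difference in means, while Kruskal-Wallis works on ranks.

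**The case against.** The strongest defence is that both branches are named in advance, so this is not a free choice after seeing results. Ranks are also a respectable analysis of a bounded scale, and the overall group test hardly suffers. All of that stands, and it limits the size of the point. It does not answer the loss of the interaction tests.

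Three stronger readings are tempting, and the documents do not support them.

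- **A successful trial tends to abandon its primary analysis.** A reader might infer this from the 93%. It needs scores near the floor. At 10 versus 6 about 73% of trials with the effect would still pass the pooled test; at 12 versus 8 nothing changes; at 14 versus 10 failure becomes rarer. The protocol excludes people with diagnosed mental health conditions, which makes lower scores plausible, but it gives no baseline mean.
- **Raw scores are wrong for every planned test.** The protocol does not say at what level the scores are tested. Tested per arm at a time point, they amount to a check of within-arm error for the one-way ANOVA. The charge holds there only if arms are pooled. For the within-person comparisons it holds at any level.
- **Arms or time points end up under different methods.** Testing all 12 arm-by-time cells would give at least one failure in about 1 − 0.95¹² = 46% of trials with perfectly normal data. But the text describes one choice between two plans. It states no cell-by-cell rule, and the testing level may be left to a statistical analysis plan that is not shown.

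**Conclusion.** The point holds in a limited form. A pretest on outcome data decides the trial's analysis. It tests the wrong quantity for the within-person comparisons, and for the one-way ANOVA if arms are pooled. It can respond to the treatment effect when scores approach zero. That last part is conditional on an assumed scale range, an assumed cut-off, pooled testing and a Control mean of roughly 10 or lower.

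No material inflation of type I error was found, and the power loss on the overall group test is at most about 4 points. The main consequence does not depend on the simulation: the analysis is not fixed in advance, and if the pretest fails, questions 7 and 8 lose the only planned test that addresses them. This should be changed, but it does not by itself invalidate the main group comparison.

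**What to change.** Rewrite the Tests for Normality paragraph:

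- Delete the Shapiro-Wilk pretest.
- Name the mean-based ANOVA-type analyses, including the two-way ANOVA interaction tests, as primary for all arms and time points regardless of normality.
- Show plots of residuals and within-person differences as description only, with no switch of method.
- Always report the planned rank-based tests beside them as a sensitivity analysis.

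Replacing the pretest with one on residuals would not be enough, because it still reacts to the effect near the floor.

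The cost is one rewritten paragraph and slightly more reporting, since both sets of tests are already planned. The downside is a mean-based primary analysis on a possibly skewed scale. The rank-based results beside it cover that for the group and time comparisons.

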**S2: Study Protocol v4 (13.09.2021)**

Study questions

*1. If practicing yoga, learning the Bhagavad Gita, or combining both reduces psychological distress, then participants in these intervention groups will show significant reductions in GAD7 scores over time compared to their baseline scores.*

*2. If the interventions are more effective than no intervention, then the GAD7 scores will be significantly lower in the intervention groups compared to the control group at post-intervention assessments.*

*3. If learning the Bhagavad Gita results in more lasting stress reduction than practicing yoga alone, then the Gita group will have lower GAD7 scores at the delayed post-intervention assessment than the Yoga group.*

*4. If combining yoga and the Bhagavad Gita has a synergistic effect, then the Yoga+Gita group will experience greater immediate and sustained reductions in GAD7 scores than either intervention alone.*

*5. If no significant changes occur in the control group over time, then the GAD7 scores in the control group will remain relatively stable across all assessments.*

*6. If the interventions differ in their sustained effectiveness, then the Gita and Yoga+Gita groups will have significantly lower DPI-GAD7 scores compared to the Yoga group at 45 days post-intervention.*

*7. Gender may moderate the effect of the interventions on psychological distress.*

*8. Educational attainment may moderate the effect of the interventions on psychological distress.*

*9. If continued practice of the interventions is important for sustained stress reduction, then participants who continue practicing the interventions will have lower GAD7 scores at the delayed post-intervention assessment than those who do not continue.*

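### Within-arm follow-up tests: single-step Bonferroni over three pairs of visits is stricter than 5% family-wise control needs, and a step-down rule would recover power at no error cost

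*Protocol*

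**What the plan says.** The first study question expects that participants in the intervention groups "will show significant reductions in GAD7 scores over time compared to their baseline scores". Under Within-Group Comparisons in the parametric plan, the Protocol answers it in two stages.

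- **Gate:** for the three visits "within each group, we will use repeated-measures ANOVA". No adjustment for unequal variances of the differences is mentioned.
- **Follow-up, only after a significant gate:** "we will conduct pairwise t-tests with Bonferroni correction", applied to every pair of visits. Baseline versus the delayed visit (DPI) is one of the two pairs given as examples. The divisor is not stated; three pairs imply 3.

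The level is general: "For all tests, a two-tailed p-value < 0.05 will be considered statistically significant". The chain applies conditionally: "If the data are normally distributed, we will proceed with parametric tests". Otherwise Friedman and Conover tests replace it.

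**The concern.** Single-step Bonferroni ignores what has been learned once one pair of visits is shown to differ. With three means, if one pair differs, at most one of the other two pairs can still be equal. Only one true null hypothesis is then left to protect, and holding the remaining tests at 0.0167 protects against errors that can no longer occur.

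The practical stake is the 45-day comparison. A large immediate change will usually pass under any rule. A change that has partly faded by day 45 is the one the extra strictness is likely to hide, and the first study question is about change over time and not only at the end of the week.

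**Working it through.** **Inputs from the Protocol.** Difference 4 points, SD 3.78, 80% power, two-sided 0.05 (Sample size); three visits and four arms; analysis of participants with all three assessments (Data exclusion). It states no sample size, within-person correlation, 45-day effect or within-arm power, so there is no figure of its own to reproduce.

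**Assumptions.** 16 completers per arm: an exact two-sample t-test on the Protocol's difference and SD gives 79.9% power at 15 and 82.5% at 16. SD 3.78 is taken as the SD of scores at each visit. Correlations (Baseline-IPI / IPI-DPI / Baseline-DPI, where IPI is the immediate visit) are 0.6 throughout, 0.8/0.5/0.5, 0.85/0.5/0.45 and 0.9/0.5/0.45. Data are normal, with tens of thousands of simulated arms per setting.

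**Rules compared, all behind the same gate.** Let p(1) ≤ p(2) ≤ p(3) be the ordered p-values of the three pairs.
- Bonferroni: every p against 0.05/3 = 0.0167.
- Holm: p(1) against 0.05/3 = 0.0167, then p(2) against 0.05/2 = 0.025, then p(3) against 0.05, stopping at the first failure.
- Shaffer: p(1) against 0.0167; if rejected, the other two against 0.05.

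No threshold of Holm or Shaffer is below Bonferroni's, so any pair Bonferroni rejects is also rejected by both.

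**What the thresholds mean in GAD7 points.** At correlation 0.6 the SD of a change is 3.78 × √(2 × (1 − 0.6)) = 3.38, and its standard error with 16 people is 3.38/√16 = 0.845. With 15 degrees of freedom:

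| Level | Critical t | Smallest significant change (points) |
|---|---|---|
| 0.0167 | 2.694 | 2.694 × 0.845 = 2.28 |
| 0.025 | 2.490 | 2.490 × 0.845 = 2.10 |
| 0.05 | 2.131 | 2.131 × 0.845 = 1.80 |

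**Validity.** With Baseline and DPI truly equal and IPI 4 points lower, the equal pair is falsely rejected in about 1.6-1.8% (Bonferroni), 4.4-5.1% (Holm) and 4.9-5.3% (Shaffer) of arms. Both step-down rules are at 5% within simulation error; Bonferroni leaves about two-thirds of the permitted error unused.

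**Power for Baseline versus DPI, immediate fall 4, 45-day fall 2.**

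| Correlations | Bonferroni | Holm | Shaffer |
|---|---|---|---|
| 0.6 throughout | 40% | 53% | 60% |
| the three unequal sets | 29-32% | 38-42% | 47-51% |

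**Gain over Bonferroni by how much of the early fall is kept (percentage points).**

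| 45-day fall after a 4-point early fall | Holm | Shaffer |
|---|---|---|
| 2 | 9-13 | 18-20 |
| 3 | 6-8 | 11-17 |
| 4 (fully sustained) | 1-3 | 2-7 |

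**The gate, separately.** With no true change, the uncorrected ANOVA rejects in about 5% of arms when sphericity holds (epsilon 1), 5.3-5.6% at epsilon 0.87-0.92, and roughly 6-7% at epsilon 0.80-0.64. Greenhouse-Geisser degrees of freedom bring this to about 4.4-5.1%. The planned chain as a whole, gate plus Bonferroni, has a family-wise error of about 2.4-3.7% with no change at any visit.

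**The case against.** **Bonferroni is a standard, prespecified and valid choice, so this is preference.** It is valid, and nothing in the Protocol contradicts it. But with the gate unchanged, Holm rejects at least as much at the same family-wise error and needs no further assumption, which makes it more than a matter of taste. Bonferroni's remaining advantage, simple matching simultaneous intervals, is not used by the plan.

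**Every size depends on assumed inputs.** This stands. The sample size, the correlations and the residual 45-day effect are not in the Protocol. At the only difference it names ("80% power to detect a minimum clinically important difference of 4 for the GAD7"), fully sustained, the gain is small.

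**A reader might infer that the plan loses up to 20 points of power for a sustained effect.** The figures do not support that. The 18-20 point gain belongs to Shaffer's rule when half of a 4-point early fall is lost by day 45.

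**A reader might also infer that the uncorrected ANOVA makes the within-arm conclusions too liberal.** It does not: gate plus Bonferroni stays below 5%. Only the omnibus p-value is affected, and 6-7% needs marked non-sphericity. The visits are 8 and 44 days apart, so sphericity cannot be presumed, but uneven spacing does not establish a marked failure. A sphericity correction is also commonly left to an SAP, which is not at hand, so its absence is not an error.

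**Adding a Greenhouse-Geisser gate is not free.** This stands. With a sustained 2-point fall under the three unequal correlation sets, about 6-12% of arms reject at least one pair under the plan but none under a corrected gate with step-down tests. The statement that nothing is lost therefore holds only with the gate left as planned.

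**Conclusion.** The point holds as a low-severity efficiency improvement. The Protocol fixes a follow-up correction that is stricter than its 5% level requires, and a better rule exists at no cost in family-wise error. The benefit ranges from 1-3 points (Holm, effect fully sustained) to 18-20 points (Shaffer, half the early fall lost), assuming 16 completers per arm, SD 3.78 for scores, and the correlations listed.

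It bears only on within-arm change, only when the parametric branch is used, and not on any between-arm comparison. It is not a finding that Bonferroni is wrong or that the planned tests have inflated error.

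**What to change.** In Within-Group Comparisons of the parametric plan, replace the Bonferroni correction with Holm's step-down correction, or with Shaffer's for three visits: the smallest of the three p-values against 0.0167 and, if it is rejected, the other two against 0.05. Name one of the two before data are seen, and keep the repeated-measures ANOVA gate as it is.

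The cost is one sentence, with no extra participants or data. The one small downside is that step-down tests have no simple matching simultaneous intervals.

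Optionally, report the omnibus test with Greenhouse-Geisser degrees of freedom so that its p-value is close to its nominal level. If the corrected test is also used as the gate, accept that some rejections are lost when sphericity fails, and that the gate is slightly conservative (about 4.4%) when it holds.

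### The main between-arm comparisons of GAD7 do not adjust for baseline GAD7, although every analysed participant has it; the test is valid but loses precision

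*Protocol*

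**What the plan says.** The protocol measures GAD7 in everyone before the interventions, one day after them and 45 days after them (Sampling Plan, Data Collection Process). For the comparison between arms, the Analysis Plan states that "at each time point (Baseline, IPI-GAD7, DPI-GAD7), we will use one-way ANOVA", followed by Tukey's HSD. If normality fails, Kruskal-Wallis and Dunn's test take their place, again separately at each time point.

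Outside its own across-arm test, baseline GAD7 is used inferentially in the within-group repeated-measures ANOVA or Friedman test, neither of which compares arms. The one place where change over time meets intervention in a model is the subgroup two-way ANOVA for gender, education and continued practice. The Variables section says that "demographic covariates (age, gender, education) will also be collected", but no main across-group test adjusts for them.

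Three other statements bear on the point:

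- Randomisation is simple, with no strata or blocks (Design Plan).
- Anyone missing one of the three assessments is excluded (Data exclusion), so baseline GAD7 is complete in the analysed set.
- The sample size is to be worked out "with 80% power to detect a minimum clinically important difference of 4 for the GAD7", "with a standard deviation of 3.78" and "at the standard alpha error of 0.05". No resulting number is given.

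**The concern.** Study questions 2, 3, 4 and 6 are contrasts between arms at follow-up, so the across-group tests answer the trial's main questions. A score taken on the same scale before treatment is usually the strongest predictor of the later score. Leaving it out keeps variance in the error term that could be removed.

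With small arms and unstratified randomisation, baseline means can also differ noticeably by chance. The plan responds with a significance test of baseline across arms. That test checks a null hypothesis that randomisation already makes true, and no action follows from its result. It neither corrects an imbalance nor recovers precision.

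At stake are the power and interval width of every between-arm contrast at both follow-ups.

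**Working it through.** **Inputs from the protocol.** Difference 4 points and SD 3.78 (Sample size); alpha 0.05 (Sample size), two-sided because "a two-tailed p-value < 0.05 will be considered statistically significant" (Analysis Plan); four arms in a 1:1:1:1 ratio (Grouping).

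**Assumptions, not in the protocol.**
- Analysed number per arm, n. There is no stated figure to reproduce. The protocol's inputs imply 16 per arm for a two-sample t-test at 80% power, or 22 per arm for one Tukey pair at 80% power. Both are shown.
- Baseline-to-follow-up correlation, rho: 0.3, 0.5 and 0.7.
- 3.78 is the SD of the raw score at each time point. The protocol does not say whether it is that or an SD of change.

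**Step 1: residual variance under ANCOVA.** Residual SD = 3.78 × √(1 − rho²). The variance factor 1 − rho² is 0.91, 0.75 and 0.51 at rho 0.3, 0.5 and 0.7.

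**Step 2: Tukey power for one pair at 4 points.** SE = residual SD × √(2/n). Error df = 4n − 4, less 1 with the covariate. Critical value = q(0.95; 4 groups, df)/√2. Power is the upper tail of a non-central t with non-centrality 4/SE. It is computed for the Tukey contrast itself, without also requiring the overall F test to be significant.

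Example, n = 16 unadjusted: SE = 3.78 × √(2/16) = 1.336; df = 60; critical value 3.737/√2 = 2.64; non-centrality 4/1.336 = 2.99; power 63.7%.

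Example, n = 16 with rho 0.5: SE = 1.336 × √0.75 = 1.157; df = 59; critical value 2.64; non-centrality 3.46; power 78.8%.

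| Analysis | Variance factor | Power, n = 16 | Power, n = 22 |
|---|---|---|---|
| Unadjusted | 1 | 63.7% | 81.0% |
| ANCOVA, rho 0.3 | 0.91 | 68.8% | 85.2% |
| ANCOVA, rho 0.5 | 0.75 | 78.8% | 92.1% |
| ANCOVA, rho 0.7 | 0.51 | 93.5% | 98.8% |

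**Step 3: interval width.** The simultaneous 95% half-width is critical value × SE. At n = 16 it is 2.64 × 1.336 = 3.53 points unadjusted, and 2.64 × 1.157 = 3.06 points at rho 0.5.

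**Step 4: chance imbalance.** The SE of a baseline difference between two arms is 3.78 × √(2/n): 1.34 points at n = 16 and 1.14 at n = 22. The probability that a given pair differs by 2 points or more (half the 4-point difference) is 13.5% and 7.9% respectively. An observed imbalance b shifts the unadjusted follow-up contrast by rho × b on average. For b = 2 that is 0.6, 1.0 or 1.4 points at rho 0.3, 0.5 or 0.7.

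**The case against.** The strongest reply is that nothing here is invalid. Under randomisation the unadjusted comparison is unbiased, and chance imbalance is already reflected in its standard error. Study questions 2, 3 and 6 ask whether follow-up scores are lower in one group than another, and the planned test addresses that directly. This stands. A reader might infer that the planned results would be biased or the type I error inflated; over all randomisations neither is true. What remains is lost efficiency, and a shift conditional on an imbalance that has actually been seen.

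A second reply is that the size of the gain is not known. This also stands. The protocol gives no sample size and no correlation. At rho 0.3 the variance falls by only 9%, and near zero there is no gain and one degree of freedom is lost. A larger gain could be shown with uncorrected pairwise t-tests or a difference below 4 points, but the protocol plans Tukey's HSD and names only 4 points.

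Two further inferences go beyond the text:

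- Because the plan says that "Partial eta-squared (η²) will be calculated for repeated measures ANOVA" and names η² for the one-way ANOVA, a reader might conclude that no estimate could be set against the 4-point difference. Tukey's HSD works on mean differences in GAD7 points, and naming η² does not rule out reporting them.
- A reader might conclude that the demographic covariates are never modelled with intervention. Gender and education do enter the subgroup two-way ANOVAs, as moderators. Only age appears in no model.

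The reply that a separate statistical analysis plan might settle this does not succeed. The protocol names the between-arm tests on both paths, so this is a choice made and not a detail deferred.

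**Conclusion.** The point holds as one of efficiency. The main between-arm tests at both follow-ups leave out a complete and probably informative covariate, on the parametric and the non-parametric path alike. For one Tukey pair at 4 points, adjustment adds about 5 to 30 percentage points of power at 16 per arm (68.8 − 63.7 to 93.5 − 63.7) and about 4 to 18 at 22 per arm (85.2 − 81.0 to 98.8 − 81.0), for rho from 0.3 to 0.7.

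These figures rest on the assumed n and rho, and on 3.78 being the SD of the raw score. If it is an SD of change, the figures move but the argument does not. The change is advisable; the trial's validity does not depend on it.

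**What to change.** 1. Make the main between-arm analysis at IPI and DPI an ANCOVA with arm as factor and B-GAD7 as covariate, or an equivalent mixed model with arm-by-time contrasts.
2. Keep the Tukey adjustment for pairwise contrasts. Report them as adjusted mean differences in GAD7 points with 95% CIs, so that they can be read against the "minimum clinically important difference of 4 for the GAD7".
3. If normality fails, replace the unadjusted Kruskal-Wallis test with a baseline-adjusted counterpart, for example rank ANCOVA, or ANCOVA with robust or bootstrap standard errors. Otherwise the problem remains on that path.
4. Drop the across-arm significance test at baseline and show baseline GAD7 descriptively, which the Analysis Plan already provides for.
5. Adjustment for age, gender or education is optional. If wanted, name the covariates in advance and allow for their degrees of freedom.

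The cost is a change of wording and one degree of freedom for the baseline covariate. No further data are needed.
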